#### Neurophysiological outcome: N400 amplitudes

At the beginning and end of each intervention phase (figure 3), brain and behavioural response (SoF) during music recognition tasks will be recorded and analysed as outcome measures. We seek to determine the N400 component related to the in-key violations (see example in figure 4) in songs learnt during the intervention period and the potential correspondence with the behavioural observations. If participants do develop musical semantic memory through our intervention, we expect them to also show an N400-like component to in-key violations in familiarised melodies, that is, those melodies that are introduced and learnt during our intervention, but only after the intervention. If an N400 component is detectable during these in-key violations of a newly learnt song, it will indicate memory of the new song even if the participant is unable to adhere to a behavioural task or display an observable SoF.

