**Figure 1 F1:**
[figure not shown]
Path diagram of hypothesised intervention mechanisms and effects.

We hypothesise that participation in an intensive, individual singing-based intervention will improve the participants’ musical semantic memory, which in turn will be associated with improved cognitive function. This effect may be mediated by positive mood (figure 1).

Furthermore, if participants with AD show an N400 component in response to unexpected in-key violation of a newly learnt melody following the proposed intervention, it would indicate that musical semantic memory—as indexed through EEG measures—can be improved.

Findings gained from this study may have implications for evidence-based treatment planning and for designing opportune interventions aiming at reducing cognitive decline and improving the quality of life of people with AD. In line with the Global Action Plan on the Public Health Response to Dementia,^30^ the present study contributes by focusing on mechanisms of memory for music, particularly in an AD population and by investigating whether musical interventions have any impact on overall cognitive functioning. Additionally, the findings could be adapted and replicated in other parts of the world to design culturally sensitive approaches for this population.

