#### Interventions

Interventions will be conducted by an instructor with adequate qualification and experience in music teaching and dementia care. Instructors will ideally have a music therapy degree, but music educators with relevant experience and training, supervised by music therapists, may also be able to conduct singing interventions for dementia.^12^ Interventions will entail individual musical training based on singing to learn 10 randomly selected songs from a list of 20 novel songs specifically created for the purposes of this study. These songs will take into consideration adequate musical complexity, length of verses and chorus and high-frequency words for the lyrics. The structure of the complete lyrics of the song will have the following sequence (similar to popular music): first verse; second verse; chorus; repetition of the first two verses; chorus; repeat chorus; final cadence.

Participants will be randomly assigned to one of the two sequences: intensive intervention phase (two sessions per week) followed by minimal intervention phase (one session per month) or vice versa (figure 2**). They will receive individual musical training based on singing during both phases**, lasting 5 months each, with 2 months of no intervention in between. During both intervention phases, participants will learn and focus the singing practice on one novel song per month. That means a total of five novel songs will be offered in each phase. The order of the songs will be randomised across the 10 months of intervention.

The instructor will use live music by singing with the support of a harmonic instrument such as piano, keyboard, guitar or accordion to deliver the musical experiences. At all times, the instructor must provide appropriate and individualised support encouraging the participant to engage in the tasks without forcing him/her to do so. It is crucial that the instructor establishes an empathic relationship with the participant for the musical experience to be pleasant, rewarding, emotionally meaningful and conducive to learning. Each session will have a duration of 40–45 min and will be conducted according to a sequence of steps^22^ as follows:

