### Outcomes

The two primary outcomes, participants’ scores on the ADAS-cog^38^ and the N400 response measured using EEG, will be assessed before and after each musical training phase (figure 3). Behavioural assessments of participants’ familiarity with the song and song performance will be conducted by the instructors in every session and by external evaluators in selected sessions at specific points of the training (last session of each month and when the instructor’s SoF rating changes). Secondary outcome measures include the behavioural assessments, participants’ self-reported mood during each intervention session and any reported adverse events.

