##### EEG protocol

Each site will collect EEG with at least 32 channels based on the 10–20 system. Preferably, active EEG systems that are less sensitive to interference from other sources will be used, which is especially important when recordings are made outside shielded rooms (eg, at participants’ homes). EEG recordings will start with a resting state measurement to familiarise participants with the situation of the EEG data collection. For the purposes of our study, a previously used paradigm^27^ is adapted to have in-key violations in familiarised/to-be-familiarised and unfamiliarised melodies only to assess reactions to memory-based knowledge. No out-of-key violations will be introduced. The in-key violations will be introduced at multiple places throughout each melody, which will consist of at least 32 bars. No violations will be introduced in the first four bars, to allow participants sufficient time to recognise the melody. A total of 10 melodies will be played for each participant, of which half are learnt in an intervention period (familiarised/to be familiarised). In each of the melodies, we will include at least eight in-key violations. ERPs in response to these in-key violations will be compared with ERPs in response to unchanged notes in structurally similar places in each melody. After each melody, applause will sound. Participants will be instructed to indicate via a button when they hear the applause. We estimate that the paradigm will last about 20 min. Half of the melodies will be and remain novel or unfamiliar, that is, they will not be introduced during the intervention. The other half of the melodies will be novel at the first EEG assessment but be introduced during the intervention and thus be considered familiarised at the second EEG assessment (familiarised/to be familiarised). At least 40 in-key violations will appear in novel melodies, and at least 40 in-key violations will appear in familiarised melodies. EEG assessments will be conducted within 7 days before the first and after the last musical training session of each intervention phase. If memory for music is gained through the intervention, we expect more pronounced N400 amplitudes to in-key violations in familiar melodies but not to in-key violations in unfamiliar melodies after the intervention. Thus, we expect an interaction effect of time (before vs after intervention period) and melody type (familiarised/to be familiarised vs unfamiliarised) on N400 amplitude variation.

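### The statements that an N400 in a taught song indicates memory leave out the never-taught melodies, which the protocol's own time-by-melody-type contrast uses as the control

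*Protocol article*

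**What the plan says.** The Outcomes section of the protocol article names two primary outcomes, the ADAS-cog and the N400 response. Three places say what an N400 finding would mean.

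- **Neurophysiological outcome: N400 amplitudes.** "If an N400 component is detectable during these in-key violations of a newly learnt song, it will indicate memory of the new song". The sentence before it says where the component is expected if memory develops: in "those melodies that are introduced and learnt during our intervention, but only after the intervention".
- **Objectives, text after Figure 1.** If participants show an N400 to an in-key change in a newly learnt melody once the intervention is over, "it would indicate that musical semantic memory—as indexed through EEG measures—can be improved".
- **EEG protocol.** "we expect an interaction effect of time (before vs after intervention period) and melody type (familiarised/to be familiarised vs unfamiliarised) on N400 amplitude variation". Here the sign of memory is a larger response after training in taught melodies and not in untaught ones. Ten melodies are played, half of them never taught, with at least 40 violations in each half. Each violation is compared with unchanged notes at matching places.

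Two other passages bear on the point. The Introduction says that an N400-like component can follow a violation of expected notes in a melody, and that its timing and origin are less firmly established for music than for language. The EEG data analysis section lets the time window and region be adjusted.

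**The concern.** The first two statements go from the presence of a response in taught songs to memory for those songs. The third requires the response to grow with training, and to grow more in taught than in untaught melodies. These conditions can disagree on the same data.

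Suppose a changed note evokes some negativity in any melody, taught or not. Taught songs then show an N400 after training, and the first two sentences allow a memory conclusion. The time-by-melody-type contrast is null. The never-taught melodies are in the paradigm to expose this case, and the presence wording does not use them. At stake is a report that people with AD formed memory for new songs, on a primary outcome, from a response that is not specific to those songs.

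**Working it through.** **The plan's own figure.** The article gives no power statement for the N400. Its ADAS-cog figure supplies the number of completers. With SD 10 and r = 0.5, the SD of the paired difference is 10 × √(2 × (1 − 0.5)) = 10, so d = 3/10 = 0.30. A two-sided 5% paired t-test needs n = 90 (power 0.804), and 90/0.8 = 112.5, rounded up to 113. Both stated numbers reproduce, and this point does not affect them. The checks below use n = 90.

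**Set-up.** Let D be a participant's violation-minus-unchanged amplitude difference, in units of its between-participant SD. D is measured in four cells: before and after training, in taught and untaught melodies. True memory is set to zero. Let g be a generic response to changed notes, equal in all four cells. The documents do not give g, so a range is assumed. All tests are two-sided at 5%.

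**Check 1: presence in taught songs after training.** This is a one-sample t-test with 89 degrees of freedom and noncentrality g√90. The contrast is (after − before, taught) − (after − before, untaught). Its expectation is (g − g) − (g − g) = 0 for any g. It was simulated with 10,000 runs per scenario, at correlations between cells of 0 and 0.5.

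| Assumed g (SD) | g√90 | Presence test positive | Contrast positive (simulated) |
|---|---|---|---|
| 0 | 0 | 5% | 5.0%–5.4% |
| 0.1 | 0.95 | 16% | not simulated; expectation 0 |
| 0.2 | 1.90 | 47% | 4.9%–5.2% |
| 0.3 | 2.85 | 80% | 4.4%–5.1% |
| 0.5 | 4.74 | 99.7% | 4.8%–5.2% |

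**Check 2: after minus before, taught songs only.** This takes the remark on timing as if it were a condition. A constant g cancels, and the simulated error is 4.6%–5.3%. Now let the response shift by h between the two recordings in both melody types alike. With uncorrelated cells the SD of the change is √2, so the noncentrality is h√90/√2: 1.34 for h = 0.2 and 2.01 for h = 0.3. The simulated error is 26% and 51%. The contrast gave 5.4% and 4.6% in the same runs.

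**Check 3: what the contrast costs.** For a true memory effect of 0.3 SD in the taught, after-training cell and no generic response, the presence test has power 0.80. The contrast has SD √(4(1 − ρ)), where ρ is the correlation between cells. For ρ = 0 the standardised effect is 0.3/2 = 0.15 and power is 0.29. For ρ = 0.5 it is 0.3/√2 = 0.21 and power is 0.51. The 0.80 here equals the false-positive rate at g = 0.3 in Check 1, because the presence test cannot tell a generic response from memory.

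**The case against.** The strongest reply is that the two sentences interpret and do not decide. One is a rationale under Objectives; the other explains why EEG helps when behaviour cannot be observed. The outcome is headed as amplitudes, the EEG protocol section names the interaction, and the Statistical analysis section compares interventions with adjustment for pre-test. No section plans a test of mere presence. This largely stands. A reader might infer that the protocol carries two rival success rules for a primary outcome. It does not: the sound contrast is already there, and the fault is in how two sentences state the inference.

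A second reply is that the N400 sentence follows a remark that the response should appear only after the intervention. That narrows the problem, since a constant generic response cancels in a before-after comparison. But the remark is a prediction of what follows if memory forms, not a condition for concluding that it did. Even as a condition it leaves the untaught melodies out (Check 2).

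A third reply is that the Introduction reports a dissociation: memory violations evoke the N400 and rule violations evoke earlier negativities, and only in-key changes are used here. That supports a small g but does not establish g = 0. The same section says it is unknown whether such memory violations evoke an N400 in AD, and the adjustable window weakens any argument from latency.

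Two stronger readings are tempting and lack support. The N400 section speaks of a participant who cannot do a behavioural task, from which a reader might infer that individuals or single songs will be labelled as remembered. No section plans this, and the neighbouring text speaks of participants in the plural. A reader might also infer, from the repeating verses and chorus of the taught songs, that repetition within a playback contaminates the response. That song form is given for the lyrics used in teaching. The EEG section says only that each melody has at least 32 bars and takes comparison notes from matching places.

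**Conclusion.** The concern holds as a fault of wording on a primary outcome. Two sentences allow memory, or improved memory, to be concluded from an N400 in taught songs without reference to never-taught melodies, while the EEG protocol section states the contrast that is needed. The design is sound.

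The size depends on quantities the documents do not give. With 90 participants and no memory, a post-only presence reading errs 5%, 16%, 47% or 80% of the time for an assumed generic response of 0, 0.1, 0.2 or 0.3 SD. A before-after reading on taught songs alone errs about 5% for a constant response. It errs 26%–51% for an assumed shared shift of 0.2–0.3 SD with uncorrelated cells. The contrast errs about 5% throughout. If there is no generic response and no shared shift, both looser readings keep their nominal error. The figures illustrate what the wording permits; they are not the error rate of a planned test.

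**What to change.** Reword the sentence in the N400 outcome section and the one in Objectives so that both point to the EEG protocol contrast, and carry the same rule into the statistical analysis plan still to be written. For example: *Memory for taught songs will be concluded, at group level, only from the change from before to after training in the violation-minus-unchanged amplitude difference in familiarised relative to unfamiliarised melodies. The presence of an N400 in taught songs will be reported descriptively.*

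This needs no new data, stimuli or recordings. The price is lower power than a presence test: about 0.29–0.51 against 0.80 for a 0.3 SD memory effect at n = 90. An N400 in taught songs with a null contrast could then not be reported as memory. That makes it worth settling the wording before any EEG results are seen. The change governs the memory conclusion only; the comparison of intensive with minimal training remains with the model in the Statistical analysis section.

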**Figure 4 F4:**
[figure not shown]
Example of a simple melody with possible places for in-key violations to detect N400 responses. Of note, actual stimuli will be novel songs specifically composed for this study, which will initially be unknown to all participants. This example of a well-known children’s song is shown for illustration purposes.

##### EEG protocol

Each site will collect EEG with at least 32 channels based on the 10–20 system. Preferably, active EEG systems that are less sensitive to interference from other sources will be used, which is especially important when recordings are made outside shielded rooms (eg, at participants’ homes). EEG recordings will start with a resting state measurement to familiarise participants with the situation of the EEG data collection. For the purposes of our study, a previously used paradigm^27^ is adapted to have in-key violations in familiarised/to-be-familiarised and unfamiliarised melodies only to assess reactions to memory-based knowledge. No out-of-key violations will be introduced. The in-key violations will be introduced at multiple places throughout each melody, which will consist of at least 32 bars. No violations will be introduced in the first four bars, to allow participants sufficient time to recognise the melody. A total of 10 melodies will be played for each participant, of which half are learnt in an intervention period (familiarised/to be familiarised). In each of the melodies, we will include at least eight in-key violations. ERPs in response to these in-key violations will be compared with ERPs in response to unchanged notes in structurally similar places in each melody. After each melody, applause will sound. Participants will be instructed to indicate via a button when they hear the applause. We estimate that the paradigm will last about 20 min. Half of the melodies will be and remain novel or unfamiliar, that is, they will not be introduced during the intervention. The other half of the melodies will be novel at the first EEG assessment but be introduced during the intervention and thus be considered familiarised at the second EEG assessment (familiarised/to be familiarised). At least 40 in-key violations will appear in novel melodies, and at least 40 in-key violations will appear in familiarised melodies. EEG assessments will be conducted within 7 days before the first and after the last musical training session of each intervention phase. If memory for music is gained through the intervention, we expect more pronounced N400 amplitudes to in-key violations in familiar melodies but not to in-key violations in unfamiliar melodies after the intervention. Thus, we expect an interaction effect of time (before vs after intervention period) and melody type (familiarised/to be familiarised vs unfamiliarised) on N400 amplitude variation.

##### EEG data analysis

EEG raw data will be converted to MATLAB-readable files and preprocessed within a standard EEG evaluation software package (e.g. EEGLAB) according to recommended processing pipelines. General EEG preprocessing steps will include bandpass filtering, artefact rejection, including the removal of noisy channels and time segments, and eye movement components identified via independent component analysis,^40^ before data epochs will be extracted for trials with or without memory violations for familiarised and unfamiliarised melodies. We will examine differences in mean amplitude in response to in-key violations and unchanged notes at six regions of interest (ROIs) based on previous research in a two-by-three grid with two levels of anterior/posterior and three levels of laterality (left, mid and right).^27 29^ The exact time window and ROI studied may be adjusted given the potential for an altered latency and amplitude of the N400 component in the participants^25^ and the use of different EEG systems between sites using cluster-based permutation tests.

### Secondary outcomes

#### Behavioural outcomes: mood, SoF and singing performance

*Mood* (Step 1 and 9 in Interventions) at the beginning and end of each session will be measured on 5-point Likert scales.

SoF with the current song will be assessed using the SoF scale,^20 37^ a 6-point Likert scale. It will be completed by the instructor at the end of each session (online supplemental Form F1) and by the external evaluator after selected sessions (online supplemental Form F3). For this study, a score of 4 or above will be considered as the threshold to determine familiarity-based recognition.

*Performance* as observed by an external evaluator based on video recordings will be analysed in selected sessions using the Participant Performance Cue Indicator Form (online supplemental Form F3). It yields a score for chorus solo (range 8–32, where 32 is best) and for chorus in context (2–8, where eight is best).

#### Adverse events

Although AEs of music interventions are rare,^41^ AE assessment is an important part of the safety aspect in all RCTs. We will ask participants or relatives at each assessment time point about the occurrence and a description of any serious or non-serious AEs. Potentially study-related serious AEs, as well as unblinded frequency counts of any AEs, will be shared and discussed with the data monitoring and safety committee (DSMC) through the trial statistician.

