## Introduction

 There are 55 million people living with dementia worldwide, and this number is expected to increase to 78 million by 2030 and 139 million by 2050.^1^ As the most common form of dementia, Alzheimer’s disease (AD) contributes to 60–80% of cases.^2^ AD is a neurodegenerative disease characterised primarily by progressive cognitive deterioration, with closely interrelated changes in emotional domains. The initial cognitive profile typically includes deficits in episodic memory, naming, semantic memory and verbal fluency.^3^ As the disease progresses, these fundamental cognitive impairments underlie and exacerbate broader symptoms, including disorientation in time and space, sleep patterns and mood, significant personality changes, communication difficulties, and motor disorders. This progressive cognitive decline eventually leads to loss of independence, with an increasing need for assistance in activities of daily living.^2^

Although cognitive symptoms typically appear years after the pathology is established in the brain,^4^ they tend to be the crucial trigger for seeking clinical attention. While these cognitive impairments represent the clinical manifestation of the disease, at the neuropathological level AD is characterised by extracellular amyloid beta plaques and intracellular neurofibrillary tangles of hyperphosphorylated τ protein. These proteins disrupt the communication between neurons, leading to neuronal loss and altered rhythmic patterns.^5^ Early cognitive impairment in AD has been linked to changes in the hippocampus, which relates to the impairment to encode new information and to retrieve it later. These biochemical changes in the hippocampus later spread to other temporal regions.^5^

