#### Step 9: session rating

After the session, the instructor will complete the remainder of the SSIF (online supplemental Form F1) to record what happened in the session, including the participant’s responses and performance, title of the intervention song, title of favourite song, duration of the session, the degree of independent evocation and SoF.^20 37^ The participant’s independent recall will be rated as follows: (a) needs full support; (b) needs intermittent support to complete each line; (c) needs support in one syllable/word per line; (d) fully independent. To record independent evocation, the instructor will indicate with an ‘X’ when the first independent recall occurs during the session, which means they will mark only one cell in the form depending on type of recall and in which repetition it occurred. If the degree of independent recall changes over the same session, the instructor will also indicate with an ‘X’ the maximum degree of independent recall where it applies. Otherwise, if remaining stable, ‘no change’ will be recorded on the SSIF.

Ratings of mood and SoF will also be analysed as outcomes (see the Behavioural outcomes section).

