### Primary outcomes

#### Cognitive outcome: ADAS-cog

Before and after each musical training phase, a neuropsychological assessment battery (ADAScog)^38^ will be administered to all participants by a trained psychometrician blinded to the intervention allocation. The scale consists of items to assess the following domains: language; memory; praxis and orientation. The standard ADAS-cog includes the following 11 subtests, with a total scoring range from 0 (no impairment) to 70 (most severe impairments): word recall (0–10); commands (0–5); naming (0–5); constructional praxis (0–5); ideational praxis (0–5); orientation (0–8); word recognition (0–12); remembering word recognition test instructions (0–5); spoken language ability (0–5); comprehension of spoken language (0–5); word-finding difficulty (0–5). The ADAS-cog score is based on the number of errors made within each subtest. Two versions will be included: one administered at baseline and at the 7-month assessment; another at the 5-month and 12-month assessments. In a retest situation, the minimum clinically important difference (MCID) is 3.^39^ The ADAS-cog takes 30–35 min to administer. The total score of the ADAS-cog at the end of each intervention will be used as the *primary clinical outcome measure*, and the scores on the 11 sub-domains as secondary clinical outcomes. We aim to administer the ADAS-cog within 7 days before the first and after the last musical training session of each intervention phase.

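### Adverse events: the only route the article describes is recall over up to five months, and the participant with AD may be the sole informant

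*Protocol article*

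**What the plan says.** The Outcomes section makes adverse events part of the secondary outcome set: "Secondary outcome measures include the behavioural assessments, participants’ self-reported mood during each intervention session and any reported adverse events". The Adverse events section then gives the collection rule: "We will ask participants or relatives at each assessment time point about the occurrence and a description of any serious or non-serious AEs". It adds that serious events possibly linked to the study, and unblinded counts of all events, go to the data monitoring and safety committee (DSMC) through the trial statistician. It describes no other route.

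The assessment times come from the ADAS-cog section, which uses two test versions, "one administered at baseline and at the 7-month assessment; another at the 5-month and 12-month assessments". The Interventions section confirms the spacing, with phases "lasting 5 months each, with 2 months of no intervention in between".

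On the informant, the Introduction says of Alzheimer's disease: "The initial cognitive profile typically includes deficits in episodic memory, naming, semantic memory and verbal fluency".

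On contact between assessments, the sequence is "intensive intervention phase (two sessions per week) followed by minimal intervention phase (one session per month) or vice versa". After each session, under Step 9, "the instructor will complete the remainder of the SSIF" (the Scoring Session Instructor Form) "to record what happened in the session". The items that Step 9 goes on to name include responses, performance, song titles, duration, recall and sense of familiarity. An adverse-event item is not among them, but the form itself is a supplement that is not shown.

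**The concern.** The collection rule has two weak features, and both stand in the text.

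- **Long recall.** One question at the end of a phase has to recover everything that happened over five months.
- **Informant.** The rule accepts either the participant or a relative. Nothing says that the relative is preferred, or that the source of the answer is recorded. The participant may therefore be the only source, and recalling events months later depends on the faculty that the Introduction calls typically impaired.

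Elsewhere the article does compensate for this. Under Baseline data, next of kin help with the language history where necessary. Under Step 1, the instructor's observation replaces self-reported mood when self-report is not possible. The adverse-event rule has no such fallback order.

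At stake are the completeness of a secondary outcome and how soon the trial team hears of a serious event. Minor or transient events are the easiest to forget over five months. For a serious event early in a phase, the described enquiry would come only at the end of that phase.

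**Working it through.** **Inputs**
- Assessment times: 0, 5, 7 and 12 months (ADAS-cog section). It is assumed that the adverse-event enquiry takes place at these same four points; the schedule in Figure 3 is not shown.
- Phases: 5 months of training, 2 months without, 5 months of training (Interventions).
- Sessions: 2 per week or 1 per month (Interventions), with four weeks per month as in Table 2.
- The article gives no adverse-event rate and no recall probability.

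**Step 1: recall windows.** 5 − 0 = 5, 7 − 5 = 2 and 12 − 7 = 5 months. The baseline enquiry precedes training, so three enquiries cover the trial period.

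**Step 2: wait from event to next enquiry, events spread evenly.** Within a training phase the mean is 5/2 = 2.5 months and the maximum is 5. Over the 12 months the mean is (5²/2 + 2²/2 + 5²/2)/12 = 27/12 = 2.25 months.

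**Step 3: instructor contact.** Intensive: 2 × 4 × 5 = 40 sessions (with calendar months, 2 × 5 × 52/12 = 43.3). Minimal: 1 × 5 = 5 sessions. If instructors also asked at each session, the mean wait would be 3.5/2, or about 2 days, in the intensive phase and 30.4/2, or about 15 days, in the minimal phase.

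**Step 4: size of under-reporting.** This cannot be derived. As an illustration only, assume that the chance of an event still being reported decays exponentially with half-life h months. The share reported at the end of a window of T months is then (1 − e^(−λT))/(λT), with λ = ln 2/h. The last column is the intensive/minimal ratio of counts that would arise if session enquiry were the only source and true rates were equal.

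| Assumed half-life (months) | Reported at 5-month enquiry | Session enquiry, intensive | Session enquiry, minimal | Ratio |
|---|---|---|---|---|
| 1 | 0.280 | 0.961 | 0.721 | 1.33 |
| 2 | 0.475 | 0.980 | 0.845 | 1.16 |
| 3 | 0.593 | 0.987 | 0.893 | 1.11 |
| 6 | 0.760 | 0.993 | 0.944 | 1.05 |
| 12 | 0.869 | 0.997 | 0.972 | 1.03 |

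Two things follow. The share reported at a 5-month enquiry runs from 28% to 87% over these assumptions, so the article cannot settle it. And session-logged counts would favour detection in the intensive phase, by a factor of 1.03 to 1.33 here, whereas the assessment enquiry covers 5 months in both phases.

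**The case against.** A reader might infer that assessments are the sole source of adverse events and that instructors do not report them. The article does not say so. Reporting between assessments, its time limits and the instructors' duties are commonly left to a full protocol or manual, and neither is shown. The list of session-form content is open-ended, so an adverse-event item may already be on the form.

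A reader might also infer that events occurring in sessions are the ones most likely to be lost. The article points the other way in part: mood is recorded at the start and end of every session, by self-report or observation, and sessions are video recorded, with selected ones rated externally. These are not adverse-event reports, but distress in a session need not go unseen.

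Third, a reader might infer that the DSMC hears of serious events only when a phase ends. The sentence on the DSMC gives no timing and is not tied to the assessment enquiry.

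Other points also stand. Relatives are named as informants. Consent comes from the participant, which limits how severe the impairment can be. The article describes adverse events of music interventions as rare. Enquiry over equal windows suits the comparison of intensities.

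All this limits the wording and the strength of the point. It leaves untouched the two features that are stated: a recall window of up to five months, and a rule under which the participant may answer alone.

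**Conclusion.** The point holds as a weakness in how a named secondary outcome is measured. The described enquiry spans up to 5 months (mean wait 2.5 months within a training phase if events are spread evenly), and a person with impaired episodic memory may be the sole informant. Under-reporting is likely and late knowledge of some events is possible. Neither is demonstrated, and the size of the loss cannot be obtained from the article.

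The documents do not support saying that events are in fact under-counted, or that the comparison of intensities is biased. With equal 5-month windows and similar recall in both phases, incomplete reporting would lower both counts alike. It is the absolute frequency that would look too low.

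The conclusion assumes that the enquiry is made at the four outcome assessments. If a route for events between assessments exists in material not shown, the concern about delay falls away once that route is stated; the informant rule would still need tightening. Sample size, power and significance level are not affected.

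**What to change.** 1. At each assessment, take the adverse-event history from a relative or caregiver whenever there is one, use the participant as an additional source, and record who answered.
2. Check the session form. If it has no adverse-event item, add one yes/no line with a description. Serious events noted between assessments should go through the existing channel to the DSMC, by way of the trial statistician, without waiting for the next assessment. If such a route already exists, state it.
3. Report session-logged events descriptively, by phase. Keep the intensive-versus-minimal comparison on the assessment enquiry, because about 40 sessions against 5 gives unequal chances of detection.

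The cost is a change to the enquiry rule and at most one line on an existing form, with no new visits or staff. The downside is slightly more recording, and session-logged counts that cannot be compared between intensities. The article expects recruitment until autumn 2026 and last assessments in October 2027, so participants still to be enrolled or followed can benefit.
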